## Abstract

**Background::**

Coronary heart disease (CHD) is an important cause of chronic heart failure, and chronic heart failure is also a serious complication in the end stage of coronary heart disease. At present, there is no specific treatment plan. Shenfu injection has advantages in the treatment of heart failure in patients with coronary heart disease, but there is a lack of standard clinical study to verify this. Therefore, the purpose of this randomized controlled trial is to evaluate the efficacy and safety of Shenfu injection combined with furosemide in the treatment of chronic heart failure in patients with coronary heart disease.

**Methods::**

This is a prospective randomized controlled trial to study the efficacy and safety of Shenfu injection combined with furosemide in the treatment of coronary heart disease and chronic heart failure. This study will be approved by the clinical research ethics committee of our hospital. The patients will be randomly divided into two groups according to 1:1:(a) Shenfu injection combined with furosemide group and (b) simple furosemide group. Standard treatment for 7 days followed up for 30 days at the same time, pay attention to its efficacy and safety indicators. The total effective rate of cardiac function improvement, left ventricular ejection fraction (LVEF), N-terminal pro-brain natriuretic peptide (NT-pro BNP), 6-minute walk test (6-MWTD), and adverse reactions will be observed. Data will be analyzed using the statistical software package SPSS version 25.0 (Chicago, IL).

**Discussion::**

This study will evaluate the efficacy and safety of Shenfu injection combined with furosemide in the treatment of coronary heart disease with chronic heart failure. The results of this experiment will provide a clinical basis for Shenfu injection combined with furosemide in the treatment of coronary heart disease and chronic heart failure.

**OSF Registration number::**

doi: 10.17605/OSF.IO/27FPM

## Introdoction

1

Chronic heart failure is a common clinical syndrome characterized by dyspnea, fatigue, and signs of volume overload, which may include peripheral edema and pulmonary rales.^[1]^ In developed countries,about 2% of adults suffer from heart failure, and the incidence increases to more than 10% in people aged 70 years and older.^[2]^ Despite the continuous improvement of treatment, chronic heart failure remains a disease with poor prognosis. In 5 years of observation, the mortality rate was 50%.^[2]^ The most important cause of chronic heart failure is coronary heart disease.^[3]^ At the same time, chronic heart failure is one of the most serious complications of coronary heart disease.^[4]^

In order to improve the symptoms and exercise abilities in patients with chronic heart failure, the guidelines developed by the European Heart Association recommend the use of diuretics,^[2]^ which can reduce the number of readmissions associated with heart failure through appropriate fluid retention management.^[5]^ In the clinic, the most commonly used diuretic in patients with heart failure is loop diuretic furosemide (furosemide). However, some studies have pointed out that furosemide has no positive effect on the prognosis of patients, and may even be related to an increased risk of hospitalization, all-cause mortality, and cardiovascular mortality.^[6]^

In recent years, Chinese medicine has shown great advantages in the treatment of chronic heart failure.^[7]^ According to the theory of TCM, the main cause of chronic heart failure is deficiency of heart Qi caused by Qi deficiency and blood stasis. Shenfu Injection (SFI) is a kind of special traditional Chinese medicine extracted from ginseng and aconite, which has the function of invigorating Qi and promoting blood circulation. SFI has shown a variety of pharmacological activities, including increased blood pressure and enhanced myocardial contractility. It has been used in China for the treatment of cardiovascular disease patients with reliable efficacy for many years.^[8]^ At present, there are no studies on the efficacy and safety of Shenfu injection combined with furosemide in the treatment of coronary heart disease with chronic heart failure. Therefore, we intend to evaluate the efficacy and safety of Shenfu injection combined with furosemide in the treatment of coronary heart disease and chronic heart failure through this randomized controlled trial.

## Materials and methods

2

### Study design

2.1

This is a prospective randomized controlled trial to study the efficacy and safety of Shenfu injection combined with furosemide in the treatment of coronary heart disease with chronic heart failure. This study will follow the Consolidated Standards of Reporting Trials (CONSORT).^[9]^ Its flow chart is shown in Figure 1.

**Figure 1 F1:**
[figure not shown]
Flow diagram.

### Ethics and registration

2.2

The protocol will be in accordance with the Helsinki Declaration and approved by the Clinical Research Ethics Committee of our hospital. This experiment has been registered in the open science framework (OSF) (registration number: doi: 10.17605/OSF.IO/27FPM). Before randomization, all patients will sign a written informed consent. and they can freely choose whether to continue the trial at any time.

### Patients

2.3

Inclusion criteria: ① meet the diagnostic criteria of coronary heart disease, the patients had occlusive myocardial infarction, and the stenosis rate of the main branch of the coronary artery (at least one branch) is more than 50%;) ② meet the diagnostic criteria for chronic heart failure.^[2]^ Doppler echocardiography indicated that the left ventricular ejection fraction was less than 50%;^[10]^③ The age was 40 to 79 years; ④ New York Heart Association (NYHA) grade III–IV; ⑤ No myocardial infarction and angina pectoris occurred in the past month.

Exclusion criteria: ① Patients with heart failure induced by other diseases such as congenital heart disease; ② Complicated with other serious diseases such as malignant tumor; ③ Other heart diseases such as severe arrhythmia; ④ Complicated with serious mental illness; ⑤ Patients with drug allergy or contraindications in this study; ⑥ Unable to understand the study protocol or unwilling to participate in the study after explanation.

### Sample size calculation

2.4

This study is a pilot clinical trial. The calculation of the sample size will be based on a drop-out rate of 20% in the clinical study, and 0.025% of the sample size will be taken as 90%, which is calculated to include 110 patients. The patient will randomly select any number from 001 to 110 from the sealed envelope and is assigned to the observation group (odd) and the control group (even) according to the parity of the number.

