### Study design

2.5

In this study, patients who meet the criteria will be screened through pre-hospital recruitments and in-hospital inpatients. The patients and their families will approve the study program and sign the informed consent form. The observation group will receive SFI (SFI 50 mg / kg CS100 ml, ivgtt, qd) combined with furosemide injection (Furosemide 20 mg / kg GS 250 ml, ivgtt, qd), while the control group will only receive furosemide injection (Furosemide 20 mg / kg GS 250 ml, ivgtt, qd). Patients in both groups will receive the same routine care and drug treatment, such as angiotensin converting enzymeinhibitiors (ACEIs) or angiotensin II receptor blockers (ARBs). If necessary, the attending physician can adjust the plan according to the patient's condition, and all interventions will be recorded in detail for final result analysis. We will set up a special drug manager, and the nurse will be responsible for preparing the medicine, preparing the solution, and using the disposable optical infusion device to infuse the corresponding numbered patients. Therefore, the study is not blind to nurses, but to researchers, patients, and statisticians. All patients will receive intravenous injections once a week. The health status of each patient will be evaluated before and after treatment, including efficacy and safety indicators, and all patients will be followed up for 30 d by telephone or outpatient clinic. Follow-up will include cardiovascular events and rehospitalization.

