## Discussion

3

Chronic heart failure is the main cause of hospitalization in the elderly worldwide, with high mortality, and has a negative impact on the quality of life in patients.^[12]^ Patients with coronary heart disease are affected by coronary arteriosclerosis, stenosis, or obstruction for a long time, which can easily cause myocardial ischemia damage, lead to heart failure, and increase mortality. Integrated traditional Chinese and Western medicine treatments are a hot spot in modern medicine.

As a traditional Chinese medicine, Shenfu injection has long been used in the treatment of coronary heart disease and heart failure in China, and has achieved good results.^[13]^ Animal studies have shown that Shenfu injection can reduce tumor necrosis factor in the blood of rats with heart failure -*α* (TNF-*α*). The therapeutic mechanism may be related to the reduction of apoptosis and the inhibition of related factors.^[14]^ A randomized controlled study confirmed that Shenfu injection can significantly improve the clinical symptoms and myocardial tolerance of patients with congestive heart failure in the acute phase, without adverse reactions.^[8]^ Since there is no standard clinical study to evaluate the efficacy of Shenfu injection combined with diuretics in the treatment of chronic heart failure in patients with coronary heart disease, we intend to evaluate its efficacy and safety through prospective randomized controlled trials.

This study also has some limitations. Due to the short planned follow-up time, we cannot understand the impact of long-term efficacy. Therefore, we may extend the follow-up time if necessary. At the same time, due to the influence of treatment methods, this study cannot be strictly double-blind, which may have a certain impact on the results.

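### The arm is the parity of the number the patient draws, so the claimed blinding of researchers and statisticians cannot be relied on if that number is used on forms or in the data

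*Protocol article*

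**What the plan says.** Allocation is described in the protocol article under 2.4 Sample size calculation: "The patient will randomly select any number from 001 to 110 from the sealed envelope". The patient then "is assigned to the observation group (odd) and the control group (even) according to the parity of the number". Odd therefore means Shenfu injection plus furosemide, and even means furosemide alone. The Abstract gives the ratio: "The patients will be randomly divided into two groups according to 1:1". Section 2.2 fixes the timing of consent: "Before randomization, all patients will sign a written informed consent".

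Section 2.5 Study design puts a drug manager in charge of supply. Nurses prepare the drug and treat patients by number, "using the disposable optical infusion device to infuse the corresponding numbered patients". From this the article draws its blinding claim: "Therefore, the study is not blind to nurses, but to researchers, patients, and statisticians".

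The Discussion adds one limitation: "due to the influence of treatment methods, this study cannot be strictly double-blind". It does not mention the numbering.

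**The concern.** Two stated rules pull against each other. Section 2.4 makes the number a complete code for the arm, with a key that takes one glance to apply. Section 2.5 uses patient numbers to run the treatment and says that three groups are blind. The infusion device is meant to hide what is being given, but it hides nothing from a person who can see whether the number is odd or even.

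The primary outcome in section 2.6 makes this matter. It is the total effective rate, built on change in NYHA class, and a shift of one class moves a patient from the invalid to the valid category. NYHA class is a clinical judgement, so an assessor who knows the arm could move the result without intending to. Under section 2.5 the attending physician may also adjust the plan, so knowledge of the arm could affect concomitant care. The Fisher exact test planned in section 2.8 cannot correct either effect.

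**Working it through.** **Inputs.** Numbers 001 to 110, and odd or even as the rule for the arm (2.4); 1:1 ratio (Abstract); patients treated by number, and blinding claimed for researchers, patients and statisticians (2.5); not strictly double-blind because of treatment methods (Discussion).

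**Step 1: the article's own ratio.** The range 001 to 110 holds 110 / 2 = 55 odd and 55 even numbers. If each number is used once, the draw gives exactly 55 to 55. The stated 1:1 ratio reproduces. Drawing without replacement is an assumption here; the article does not state it, but the ratio implies it.

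**Step 2: what the number reveals.** The arm is a fixed function of the number. A person who knows the rule and sees the number is right for 110 of 110 numbers. This restates the rule and does not measure an effect. It becomes a loss of blinding only for people who hold both the rule and the number.

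**Step 3: comparison with ordinary predictability.** Suppose someone sees no numbers but knows all past assignments and the 55/55 totals, and always guesses the arm with more places left. With n = 55 per arm, the expected number of correct guesses is

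n + (4^n / C(2n, n) − 1) / 2 = 55 + (4^55 / C(110, 55) − 1) / 2 = 61.1,

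and 61.1 / 110 = 55.5%, against 50% for pure chance. The exposure therefore comes from the number itself, not from the pool of numbers running down.

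**Step 4: who holds both the rule and the number.**

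| Group | Knows the rule? | Sees the number? | Position |
|---|---|---|---|
| Nurses | Not needed | Yes (2.5) | Openly unblinded |
| Researchers and assessors | Yes, it is in the protocol | If it is on forms or in the database, to which 2.7 gives researchers access | Arm readable |
| Statisticians | Yes, from the protocol | If it is in the dataset | Arm readable |
| Patients | Only if told, or if they read it | Yes, they draw it | Arm readable only if they know the rule |

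**Step 5: does the caveat cover it?** The Discussion gives the treatment methods as the reason why blinding is incomplete. That reason concerns administration. It does not extend to a statistician or an off-ward assessor who never sees the infusion but does see a number.

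**Step 6: the draw itself.** Envelopes are sealed and consent comes first, so before the draw the arm is largely unforeseeable (step 3). The patient takes any number, however, and not the next one in a sequence. No expected order of numbers by enrolment exists, so a departure from procedure could not be seen by comparing the two.

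**The case against.** The strongest reply is that the article never says that the drawn number stays with the patient on assessment forms or in the dataset. Only one phrase, about infusion, links the number to later use, and a condensed article may leave dataset coding to the full protocol. This stands as a limit on the point. Continued use of the number is the natural reading, because no other patient number is defined, but it is an inference.

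A reader might go further and infer that the numbering unblinds everyone. The documents do not support that. Nurses are already unblinded by design. A patient learns nothing from the number without knowing the rule. Controls receive furosemide only, with no matching infusion for Shenfu described, and the Discussion concedes that the trial is not strictly double-blind. Part of the loss of blinding therefore has another cause, and neutral numbers would not cure it.

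A reader might also infer that unwelcome draws will be returned and repeated, giving selection bias at entry. Nothing in the text permits a redraw, and custody and logging of envelopes are details that an article commonly omits. Only the observation in step 6 survives.

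Finally, a reader might count the lack of stratification by NYHA class as a fault. Unstratified 1:1 randomization is valid and the article claims nothing else, so stratification would be a preference.

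**Conclusion.** The point holds in a limited form. The parity rule in 2.4 and the blinding claim in 2.5 conflict for researchers and statisticians, and the caveat in the Discussion does not resolve the conflict. The conclusion rests on one assumption: that the drawn number, the only one defined, is what appears on assessment forms or in the dataset. If so, the arm can be read for all 110 patients by anyone in those groups. If a separate neutral number is used, the article needs to say so and the exposure largely disappears.

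The effect on the treatment estimate cannot be calculated from the documents. The point is still worth settling before the first patient enters, because knowledge of the arm during the rating of a clinician-judged primary outcome cannot be repaired in the analysis. The lack of a fixed enrolment order is a secondary weakness. No sample-size or error-rate figure changes.

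**What to change.** 1. Replace the parity draw with a pre-generated random 1:1 list, held by the drug manager already planned in 2.5 and assigned strictly in order of enrolment, after consent. One list of 55 and 55 keeps the ratio if all 110 are enrolled. Small fixed blocks are not needed and would be easier for unblinded staff to predict: for known blocks of 4 the same formula gives 2 + (16/6 − 1)/2 = 2.83 correct of 4, or 71%, against 55.5%.
2. Give patients sequential study numbers that carry no arm information, and use only these on assessment forms and in the dataset.
3. Release data to the statistician with the arms under neutral codes A and B.
4. Limit the blinding claim in 2.5 to those whom it can cover, namely outcome assessors and statisticians, so that it agrees with the Discussion.

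The cost is a few hours to generate the list and relabel, plus revised wording in 2.4 and 2.5. No extra patients or staff are needed, and the tests in 2.8 can stay as they are.

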### Study design

2.5

In this study, patients who meet the criteria will be screened through pre-hospital recruitments and in-hospital inpatients. The patients and their families will approve the study program and sign the informed consent form. The observation group will receive SFI (SFI 50 mg / kg CS100 ml, ivgtt, qd) combined with furosemide injection (Furosemide 20 mg / kg GS 250 ml, ivgtt, qd), while the control group will only receive furosemide injection (Furosemide 20 mg / kg GS 250 ml, ivgtt, qd). Patients in both groups will receive the same routine care and drug treatment, such as angiotensin converting enzymeinhibitiors (ACEIs) or angiotensin II receptor blockers (ARBs). If necessary, the attending physician can adjust the plan according to the patient's condition, and all interventions will be recorded in detail for final result analysis. We will set up a special drug manager, and the nurse will be responsible for preparing the medicine, preparing the solution, and using the disposable optical infusion device to infuse the corresponding numbered patients. Therefore, the study is not blind to nurses, but to researchers, patients, and statisticians. All patients will receive intravenous injections once a week. The health status of each patient will be evaluated before and after treatment, including efficacy and safety indicators, and all patients will be followed up for 30 d by telephone or outpatient clinic. Follow-up will include cardiovascular events and rehospitalization.

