### Evaluation criteria and efficacy judgment

2.6

1.Main outcome measures: ① total effective rate of cardiac function improvement (refer to the guiding principles of clinical research of new drugs in traditional Chinese medicine^[11]^), Excellent: heart failure was essentially ameliorated or the NYHA classification increased by at least 2 levels; Valid: NYHA classification increased by 1 level; Invalid: NYHA classification remained the same before and after the treatment. Worsened: NYHA classification decreased by at least.2.Secondary outcome measures: left ventricular ejection fraction (LVEF), N-terminal pro-brain natriuretic peptide (NT-pro BNP), tumor necrosis factor-*α* (TNF-*α*), Interleukin-6(IL-6), and 6-minute walk test.3.Adverse reactions, including abnormal liver and kidney function and any discomfort during treatment (such as dizziness, nausea, etc.).

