### Data collection and management

2.7

Data will be collected before treatment, 72 hours after treatment, and at the end of treatment according to evaluation criteria. After 30 days of treatment, outpatient or telephone follow-up will be conducted for each patient. Detailed follow-up information can not be collected to record the reasons for loss of follow-up information. All data will be collected by one or two assistants. Personal information about potential and registered participants will be collected, shared, and kept in a separate storeroom to protect confidentiality before, during, and after the trial. Access to the database will be limited to the researchers of this research group.

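### Section 2.5 calls patients and researchers blind, but the unequal infusions and the odd/even patient number can reveal the arm, leaving the judged NYHA primary outcome open to bias

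*Protocol article*

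**What the plan says.** Section 2.5 of the protocol article closes its account of drug preparation with the claim "Therefore, the study is not blind to nurses, but to researchers, patients, and statisticians". The treatments are given a few sentences before: "The observation group will receive SFI (SFI 50 mg / kg CS100 ml, ivgtt, qd) combined with furosemide injection", whereas "the control group will only receive furosemide injection". The furosemide infusion is the same in both arms (250 ml carrier), and the Shenfu infusion has its own 100 ml carrier. The masking measures named are a drug manager, preparation by the nurse, and "using the disposable optical infusion device to infuse the corresponding numbered patients".

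Under section 2.4 the patient draws a number between 001 and 110 and "is assigned to the observation group (odd) and the control group (even) according to the parity of the number".

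The primary outcome in section 2.6 is the total effective rate, graded mainly by change in NYHA class, for example "Valid: NYHA classification increased by 1 level". Section 2.7 says of data collection that "All data will be collected by one or two assistants". It does not say who grades NYHA class or whether that person is kept apart from treatment.

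The Discussion concedes that "this study cannot be strictly double-blind, which may have a certain impact on the results".

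**The concern.** The blinding claim does not follow from the measures described. An add-on infusion without a matching dummy is visible to the patient and to anyone at the bedside. A number whose parity gives the arm is legible to anyone who knows the rule, even away from the bedside.

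This matters because of the outcome. NYHA class is a clinical judgement, and one class separates an invalid result from a valid one. If the patient or the grader knows the arm and expects Shenfu to help, the total effective rate can move in its favour with no drug effect. The attending physician may also adjust treatment, so knowledge of the arm could affect co-treatment as well. A significant result could then not be attributed to Shenfu, and the trial report would carry a blinding statement that its own methods section undermines.

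**Working it through.** **Step 1: infusions against the blinding claim (section 2.5).**
- Observation arm: Shenfu in a 100 ml carrier plus furosemide in a 250 ml carrier, so two infusions.
- Control arm: furosemide in a 250 ml carrier, so one infusion. None is described in place of Shenfu.
- Masking device: if optical means light-shielding (an assumption), it hides colour. It does not hide the number of infusions or the extra volume.
- Result: as described, the patient and bedside staff can tell the arms apart. Section 2.5 gives a daily regimen but also speaks of weekly injections. That must be reconciled, but this step does not depend on it.

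**Step 2: patient number against the blinding claim (sections 2.4 and 2.5).**
- Odd is observation and even is control. Infusions are matched to patients by number.
- If the same number labels the outcome forms or the analysis file, a grader or statistician who knows the rule can read the arm without seeing an infusion.

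**Step 3: illustration of what a grading shift would do.** The article gives no effective rates, so it has no figure of its own to reproduce here.

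Inputs from the article:
- Numbers 001 to 110, half odd and half even: 110 / 2 = 55 per arm.
- Drop-out of 20%: 55 × 0.80 = 44 per arm.
- Fisher exact test at P < .05 (section 2.8), taken as two-sided.

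Assumed inputs: an effective rate p of 70% in both arms (60% as a check), no true effect, and a shift d of 0, 5, 10 or 15 points from invalid to valid in the Shenfu arm only.

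Formula, summing over all pairs a, b from 0 to n:

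P(reject) = Σₐ Σ_b Bin(a; n, p + d) × Bin(b; n, p) × 1[Fisher P(a, b) < 0.05]

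| n per arm | p | d = 0 | d = 5 | d = 10 | d = 15 |
|---|---|---|---|---|---|
| 44 | 70% | 2.8% | 4.9% | 12.7% | 29.4% |
| 44 | 60% | 2.9% | 5.0% | 11.9% | 25.1% |
| 55 | 70% | 3.1% | 6.0% | 16.8% | 38.4% |
| 55 | 60% | 3.0% | 5.7% | 14.8% | 32.1% |

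The first entry is 0.02847 before rounding. Without bias the test is conservative, as Fisher's test usually is. A 5-point shift leaves rejection near the nominal 5%, and a 10-point shift takes it to two to three times nominal or more. The 55-per-arm rows are closer to the full analysis set named in section 2.8; the 44-per-arm rows are a completers view.

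**The case against.** The other side can fairly say four things.

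1. **A reader might infer that the Discussion flatly contradicts section 2.5.** It does not. Section 2.5 already says nurses are not blind, and that alone makes a trial less than strictly double-blind. The Discussion also discloses a possible effect on results. This stands: the firm inconsistency lies between the blinding claim and the infusions and numbering in sections 2.4 and 2.5. But the Discussion does not resolve it, because it never says that patients may know their arm.

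2. **A reader might infer that researchers and graders are shown to be unblinded.** They are not. Nothing says the assistants attend infusions or that the attending physician grades NYHA class. Masked grading may already be intended. This stands as a limit: for graders, the documents support an open route (the parity of the number), not proof that it is used.

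3. **A dummy infusion might appear in a full protocol that is not shown.** The word only in the control regimen makes this unlikely, but the accurate statement is that none is described. Condensation does not excuse the article, since it makes a positive claim that its own description fails to support.

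4. **The size is assumed.** This stands in full. No base rate or shift comes from the article, and a small shift does little.

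**Conclusion.** The point holds as an inconsistency in the methods: patient and researcher blinding is asserted, while the described infusions and the odd/even numbering do not secure it. That conclusion needs no assumption about rates. It rests on there being no dummy infusion beyond what is described, on the optical device being at most light-shielding, and, for graders and statisticians, on the allocation number being visible to them.

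The consequence is that a judgement-based primary outcome is exposed to expectation and assessment bias. How large that bias would be cannot be estimated from the article. The table shows only what assumed shifts would do, from almost nothing at 5 points to false rejection of 25% to 38% at 15 points. It is not an estimate of this trial's error rate. The plan should be corrected, but the article does not show that the result will be biased.

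**What to change.** - **Wording.** Correct section 2.5 to say that patients, nurses and bedside staff cannot be regarded as blinded, and align the Discussion with it.
- **Grading.** Name one of the already planned data-collection assistants to grade NYHA class at baseline and at the end of treatment. This person does not attend infusions or see treatment charts.
- **Numbers.** Use study numbers unrelated to the odd/even allocation on the NYHA forms, for LVEF and laboratory readings, and in the analysis file.
- **Interpretation.** Report NT-proBNP and LVEF as the secondary outcomes they already are, and read the NYHA result alongside them. I would not make NT-proBNP agreement in direction a condition of success. It would be a new criterion with no threshold. If NT-proBNP were unaffected and independent of grading (assumed), its direction would agree about half the time, so 12.7% would fall only to about 12.7% × 0.5 = 6.4%.

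Whether a dummy infusion is acceptable is a question for the clinicians.

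Cost: no extra patients, visits or tests. One assistant's tasks must be kept apart from treatment, which is a real constraint when only one or two are planned. The report can claim assessor blinding only. A masked grader does not remove the patient's own expectation, and a patient may disclose the second infusion, so both must be stated as limitations.

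### Section 2.5 orders daily infusions in both arms and then weekly injections for all patients, and the 72-hour visit and the 30-day follow-up have no stated starting point

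*Protocol article*

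**What the plan says.** **Frequency.** Section 2.5 (Study design) marks every infusion qd. The observation group's Shenfu entry reads "SFI 50 mg / kg CS100 ml, ivgtt, qd", its furosemide entry is also qd, and "the control group will only receive furosemide injection (Furosemide 20 mg / kg GS 250 ml, ivgtt, qd". Later in the same paragraph comes: "All patients will receive intravenous injections once a week".

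**Duration.** Only the abstract (Methods) gives a number of treatment days: "Standard treatment for 7 days followed up for 30 days at the same time". Sections 2.5 and 2.7 give none.

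**Assessments.** Section 2.7 (Data collection and management) states: "Data will be collected before treatment, 72 hours after treatment, and at the end of treatment according to evaluation criteria".

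**Follow-up.** Section 2.5 says that "all patients will be followed up for 30 d by telephone or outpatient clinic" and that this covers cardiovascular events and readmissions. Section 2.7 words it differently: "After 30 days of treatment, outpatient or telephone follow-up will be conducted for each patient".

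**The concern.** The frequency and number of infusions define the treatment being compared. One paragraph states two frequencies that cannot both apply, and the methods give no course length that would help a reader choose between them. Section 2.5 has nurses prepare and give the infusions, and section 2.3 admits patients in NYHA class III or IV, so an unclear schedule is a safety matter as well as a matter of definition. Section 2.5 also lets the attending physician adjust the plan, with all interventions recorded for the final analysis. An adjustment can be recognised as one only against a single planned schedule.

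Timing matters for the outcomes too. The main outcome in section 2.6 compares NYHA class before and after treatment, so its second measurement depends on when treatment ends. Cardiovascular events and readmissions are collected over 30 days, and which events fall inside that window depends on when it opens.

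**Working it through.** The article states no number of infusions, so there is no figure to reproduce. The check counts infusions under each stated frequency and then places the time points on a calendar.

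**1. Infusions per patient**

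Inputs: course length D = 7 days (abstract); once daily or once a week (both section 2.5).

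- Daily: infusions = D = 7.
- Weekly, given on days 1, 8, 15 and so on up to D: only day 1 falls within 7 days, so infusions = 1.
- Ratio: 7 / 1 = 7.

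**2. The 72-hour visit**

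72 hours / 24 = 3 days. The first infusion is on day 1, the 7-day course ends on day 7, and the list in section 2.7 is taken to be in time order.

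- Counted from the first infusion: day 1 + 3 = day 4, before the end of treatment, which fits the order of the list.
- Counted from the end of treatment: day 7 + 3 = day 10, after the end of treatment, which does not fit.

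The order therefore rules out the end of treatment as origin. It leaves the first infusion or some other infusion, and the text does not say which.

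**3. The 30-day follow-up**

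Three statements bear on it:

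- Abstract: 7 days of treatment and 30 days of follow-up, linked by a phrase that suggests they start together.
- Section 2.5: 30 days of follow-up, no start given.
- Section 2.7: contact after 30 days of treatment. Taken literally this does not fit a 7-day course; it may mean 30 days after treatment.

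With a 7-day course:

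- Start at the first infusion: days 1 to 30.
- Start when treatment ends: days 7 + 1 = 8 to 7 + 30 = 37.
- Days common to both: 8 to 30, that is 30 − 8 + 1 = 23 of 30.

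Events on days 1 to 7 count under the first reading only, and events on days 31 to 37 under the second only.

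**The case against.** The strongest reply is that the intended plan can be recovered. The 7 days in the abstract and the three qd entries in section 2.5 agree with each other, and a 72-hour assessment fits midway through such a course. Only one sentence disagrees, and it may be loose wording for a one-week course. On this view the end of treatment is day 7 and baseline is plain. The abstract and section 2.5 both treat the 30 days as follow-up, and section 2.7 itself attaches them to outpatient or telephone contact.

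Much of this stands. The 7 days do not conflict with daily infusion, baseline is anchored, and the end of treatment is day 7 if the abstract governs. But the text nowhere says that the weekly sentence is a slip, and it is an explicit statement about all patients. Nor does the reply supply the origin of the 72-hour visit or the start of the follow-up.

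A second reply is that a journal article condenses a fuller protocol. That would excuse a schedule left out. Here the schedule is stated, in two incompatible ways. It is also true that the article does not say the nurses work from this text, so the safety risk is a reasonable inference and not something the document shows.

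**Conclusion.** The point holds for the infusion frequency and for two time origins. Daily and weekly administration are both prescribed, and over the 7 days in the abstract they mean 7 and 1 infusions per patient. The 72-hour visit has no stated origin. The follow-up window could open at the first infusion or at the end of treatment, a shift of 7 days if the course lasts 7 days. These sizes rest on the abstract's duration governing and on the list in section 2.7 being in time order.

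Four stronger readings are tempting but not supported:

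- *Exposure differs at least sevenfold however the text is read.* Sevenfold belongs to the 7-day course and is not a lower bound. A literal 30-day course would give 30 daily infusions against 5 weekly ones (days 1, 8, 15, 22, 29), and 30 / 5 = 6.0.
- *Treatment lasts 30 days.* This needs a literal reading of one phrase in section 2.7. The abstract and section 2.5 make the 30 days follow-up.
- *No assessment is anchored.* Baseline is, and so is the end of treatment if the abstract governs.
- *The diluents CS and GS contradict each other.* CS is printed for Shenfu injection and GS for furosemide, which is written the same way both times.

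A secondary point concerns the dose notation. The / kg printed in front of each diluent reads literally as a per-weight unit. No passage gives a different dose, so this is not a contradiction, but it should be confirmed in the same step.

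**What to change.** Before the first patient is enrolled, the investigator and the drug manager should:

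1. Reconcile the abstract with sections 2.5 and 2.7 into one statement of infusion frequency and number of treatment days, and put it in section 2.5.
2. Confirm in that statement whether / kg is a per-weight unit.
3. Give the 72-hour visit, the end-of-treatment assessment and the 30-day follow-up each a named origin, and use the same origin wherever the follow-up is mentioned.

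Which frequency or dose is right is for the investigators to settle; none is proposed here.

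The cost is a protocol clarification and a notification to the ethics committee. No extra patients, visits or procedures are needed.
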